## 3. Data Security

The study will be conducted in accordance with the Helsinki Declaration [48]. Ethical approval to conduct this study was obtained from four relevant ethical committees. Study participants will be required to sign written informed consent prior to enrollment after the aim and objectives of the study have been explained and accepted by the participant, and participants will be provided with a copy of the consent form for future reference. Tape-recorded information and written data collected from participants on questionnaires will be stored appropriately in a lockable cabinet with restricted entry. Data obtained will also be captured in statistical software on a password-protected laptop. The transfer of data across the research team will occur via an encrypted flash drive or a secure file transfer protocol. Information provided by participants will be kept anonymous. Data will be kept anonymous during the study and will be kept strictly confidential in storage for two years after the completion of the study within the University of KwaZulu Natal. During the dissemination of the findings, no identifying data will be made public. Therefore, the researcher will take responsibility to ensure that, even after all information has been collected, sources will never be identified.

## 4. Discussion

The aim of this study is to adapt an HEP for improving the uptake of HIVST by men in Rwanda. To the best of our knowledge, this study is the first of its kind in Rwanda. Given the reported low uptake of HTSs among men in Rwanda, and in Sub-Saharan Africa in general, implementing an effective HEP to improve the uptake of HIVST, a new intervention with reported acceptability among men, may help bridge this gap. The pragmatic approach is designed to provide results that are directly applicable to normal practice.

Several studies have called for the need for the implementation of policies that advocate for men’s health [49,50,51]. Tailored HEPs to improve men’s uptake of HTSs have been recommended [52]. As HIVST is relatively new in Rwanda [11], there is need for the implementation of guidelines and policies that advocate for men’s engagement in this new intervention and for the scaling up thereof [53]. The knowledge obtained by the present study may thus guide HIVST implementation in Rwanda with the potential of being further incorporated into routine practice.

Consistent with the nature of pragmatic trials, we aim to influence policy by providing stakeholders with results that are applicable to routine practice. We intend to disseminate findings of the study through reports, publications in peer-reviewed journals, research meetings, and conference presentations.

Due to constraints of time and resources, as this study is for a doctoral degree with limited findings, a pilot RCT will be used to assess the preliminary effects of the HEP. A pilot study is not a hypothesis testing study. However, a pilot study is a requisite initial step, and results can inform feasibility and identify modifications needed in the design of a larger ensuing hypothesis-testing study. In this study, the feasibility of recruitment, intervention implementation, and retention will be examined. Secondly, due to the nature of the HIVST being conducted privately, study outcomes will be based on self-reported data. Finally, the HIVST uptake is only as important as the number of individuals actively linked to care and treatment services. The proposed study will not actively follow up on participants for linkage to care and treatment services. However, sufficient information on linkage to care post-HIVST will be provided on both enrollment and follow-up visits.

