Intervention: The intervention will be presented at the end of Phase 3 of the study. It will be a male-tailored HEP aimed at improving the uptake of HIVST among men. This will be delivered through face to face personal communication with the use of information education communication materials. We anticipate the HEP to address general information on HIV, transmission, prevention, HIVST, anti-retroviral therapy, and care in a manner that is tailored to men.

Randomization procedure: Simple randomization using a randomization table created by a computer software program will be employed.

Blinding: For the purposes of this study, there will be no masking. 

Data Source: We will employ an interviewer-administered questionnaire to collect data.

Analysis: Proportions will be calculated for the uptake of HIVST for both control and intervention groups. KAP scores will be calculated by determining the average score for each individual for each category of KAPs that will be assessed. Tables and graphs will be used where appropriate to present results. Quantitative variables will be summarized by means and standard deviation (SD). Qualitative variables will be summarized using frequency distribution. The student t-test or analysis of variance (ANOVA) will be used to compare if there are differences in KAP scores between different categories of the factor variables. Linear regression will be utilized to determine the association between KAP scores and quantitative factor variables. Multiple logistic regression will be used to determine the association between the uptake of HIVST and the use of HEP whilst adjusting for other study variables. All statistical tests will be concluded at a 5% level of significance. All statistical analysis will be carried in the Stata version 16 statistical package.

Primary outcome(s): The feasibility of a larger RCT trial will be assessed by recruitment and the uptake of HIVST Uptake of HIVST will be measured as self-reported use of a HIVST kit at follow-up interview. 

Secondary outcome(s): Secondary outcome variables will include HIV diagnosis among participants, linkage to care for men who tested positive for HIV, a repeat test from men who tested negative for HIV, and HIV status disclosure to sexual partner(s) post-HIVST.

Table 3 summarizes the outcomes, exploratory factors, and the methods of analysis for each study objective.

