**Phase 4: Objective 5 To determine preliminary impact of the HEP on uptake of HIVST among men in Rwanda**			
- Recruitment - Uptake (self-reported use of the HIVST kit)	- 60 men followed after 3 months - At least 80% will take up HIVST	- Percentage response rate - Proportion of men who will take up HIVST	Descriptive statistics or estimates based on 95% confidence intervals (CI)
% of men who get HIV diagnosis	Higher proportion of HIV diagnosis, linkage to care, and repeat testing for negative participants in the intervention group (HEP), compared with the non-intervention group.	Age, education level, religious belief, sexual behavior, sexual preference, marital status; age of first sexual encounter; the number of sexual partners, the history of STI, circumcision, condom use, alcohol and drug use, perceived risk of contracting HIV, level of income, distance to the point of sale of HIVST	Logistic regression
% of men who tested HIV positive and linked to care			
% of repeat test from men who tested HIV negative			

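### Table 3's success hypothesis of higher linkage to care in the HEP arm cannot be supported: linkage would be unverified self-report from about 1 to 3 positive men in total

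*Protocol article*

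**What the plan says.** Section 2.9 (Phase 4) lists among the secondary outcomes "linkage to care for men who tested positive for HIV". Table 3, under Objective 5, gives the variable as the percentage "of men who tested HIV positive and linked to care" and attaches a directional criterion: "Higher proportion of HIV diagnosis, linkage to care, and repeat testing for negative participants in the intervention group (HEP), compared with the non-intervention group". Logistic regression is the method named for this block of outcomes, beside a long list of exploratory factors.

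On data collection, section 2.9 says "We will employ an interviewer-administered questionnaire to collect data", states that there is no masking, and requires men to be willing to be followed up three months after enrollment. The Table 3 recruitment target is "60 men followed after 3 months".

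The Discussion, among its limitations, says that "study outcomes will be based on self-reported data" and then "The proposed study will not actively follow up on participants for linkage to care and treatment services". The next sentence adds that "sufficient information on linkage to care post-HIVST will be provided on both enrollment and follow-up visits". The same paragraph says that a pilot does not test hypotheses.

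**The concern.** Three parts of the article treat linkage differently. Section 2.9 makes it an outcome. Table 3 makes it a comparative success criterion with a regression. The Discussion disclaims active follow-up for it and says the pilot does not test hypotheses. The sentence after the disclaimer is about giving men information, not about collecting it, so the reader has to infer how linkage status would be recorded.

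This matters because the Discussion itself says that uptake of self-testing is worth only as much as the linkage that follows, and because the study aims to inform policy. If Table 3 is followed as written, the report will say whether the HEP arm met a linkage criterion. That statement would rest on a very small number of men and on what they say to an interviewer in an unmasked trial.

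**Working it through.** The article states no sample size, power or event count for linkage, so there is no figure to reproduce. The check asks how many positive men the article's own figures imply.

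**Inputs**
- Men followed at three months: 60 (Table 3), read as the total for both arms.
- Uptake: 80% (Table 3 criterion), applied to both arms.
- HIV prevalence in men: 2.2% national, 4.4% Kigali, 6.0% Nyarugenge, the trial hospital's district (section 2.3).
- Assumptions: the arms are equal in size, and these prevalences apply to men who do not know their status. The article gives no figure for that group. Eligibility removes men who know they are positive and also men who know they are negative, so the direction of any error is not known.

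**Formulas**
- Testers: 60 × 0.80 = 48, or 24 per arm.
- Expected positive men in total: 48 × p.
- Probability that one given arm has none: q = (1 − p)^24.
- Probability that at least one arm has none: 1 − (1 − q)².

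| Prevalence p | Expected positives, both arms | q | At least one arm has none |
|---|---|---|---|
| 2.2% | 48 × 0.022 = 1.06 | 0.586 | 83% |
| 4.4% | 48 × 0.044 = 2.11 | 0.340 | 56% |
| 6.0% | 48 × 0.060 = 2.88 | 0.227 | 40% |

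If all 60 men test (30 per arm), expected positives are 1.32, 2.64 and 3.60, and the last column becomes 76%, 45% and 29%.

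**What a comparison could show.** If an arm has no positive man, its percentage linked has no denominator and the arm effect in the regression cannot be estimated. If both arms have some, take the most extreme result, all linked in one arm and none in the other. With k positives per arm the two-sided Fisher p is 2 / C(2k, k):
- k = 2: 2/6 = 0.33
- k = 3: 2/20 = 0.10
- k = 4: 2/70 = 0.029

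So 8 positive men, evenly split and perfectly separated, are the first equal split to pass the 5% level. That is 8/48 = 16.7% of testers, against a highest quoted prevalence of 6.0%. If the 60 were meant per arm, testers double to 96 and expected positives to 96 × 0.022 = 2.1 up to 96 × 0.060 = 5.8, still short of 8.

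If the percentage were taken over all men in an arm, the number linked would still be capped by the same few positives.

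**The case against.** The strongest reply is that the passages do not contradict each other. Men are interviewed at three months, outcomes are declared to be self-reported, and a positive man can be asked then whether he went to care. Declining active follow-up for linkage reads naturally as no tracing or verification, and the next sentence contrasts that with giving information. The article also discloses both limits, and details such as questionnaire items can be left to documents not shown.

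Most of this stands. A reader might infer from the Discussion that the study cannot establish who was linked. The documents do not support that, because the planned interview is a route to the answer. A reader might also argue that positive men who never return would inflate the percentage. The 60 in Table 3 are men already followed, so non-returners lie outside that base. The article gives no rate of non-return or of non-disclosure at interview, so neither the direction nor the size of such a bias can be shown.

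What the reply does not answer is Table 3. Admitting self-report and disclaiming hypothesis testing in the Discussion does not remove a directional criterion and a regression from the analysis table. The small denominator would defeat that comparison even with perfect clinic records.

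**Conclusion.** The point holds as a mismatch between the linkage comparison in Table 3 and what the pilot can deliver. Linkage would be self-reported, untraced and unmasked, and known only for men who return and report a positive result. On the article's own figures about 1 to 3 such men are expected in total, and at least one arm would have none with probability between 40% (prevalence 6.0%) and 83% (prevalence 2.2%).

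The result rests on 60 being the trial total, 80% uptake in both arms, equal arms, and the quoted prevalences holding for men of unknown status. Full uptake or a doubled sample changes the numbers but not the conclusion. This is a secondary outcome of a pilot, so the point is worth correcting but does not threaten the trial as a whole.

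**What to change.** Make section 2.9, the Discussion and Table 3 agree:

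1. In section 2.9 and Table 3, rename the outcome 'self-reported linkage to care at the three-month interview (not traced or verified)'.
2. Report it descriptively, as counts by arm of men reporting a positive test, with linked, not linked and unknown shown separately.
3. Remove linkage from the between-arm success hypothesis and from the logistic regression in Table 3.
4. In the Discussion, add that linkage is recorded from the interview only, so that the existing limitation and the outcome say the same thing.

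The cost is wording only, with no extra visit, staff or tracing. The downside is a weaker stated claim about linkage, which is the claim the pilot can support.

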## Figures and Tables

**Table 1 medicina-56-00149-t001:** Consolidated framework for implementation research.

Intervention Characteristics
(a) Intervention source: Perception of key stakeholders about whether HIVST externally or internally developed.
(b) Evidence Strength and Quality: Stakeholders’ perceptions of the quality and validity of evidence supporting the belief that HIVST will have desired outcomes.
(c) Relative advantage: Stakeholders’ perception of the advantage of implementing HIVST versus an alternative solution
(d) Adaptability: The degree to which HIVST can be adapted, tailored, refined, or reinvented to meet local needs
(e) Trialability: The ability to test HIVST on a small scale in the organization, and to be able to reverse course (undo implementation) if warranted.
(f) Complexity Perceived difficulty of implementation, reflected by duration, scope, radicalness, disruptiveness, centrality, and intricacy and number of steps required to implement
(g) Design Quality and Packaging Perceived excellence in how HIVST bundled, presented, and assembled
(h) Cost: Costs of HIVST and costs associated with implementing HIVST including investment, supply, and opportunity costs.

**Table 2 medicina-56-00149-t002:** Calculation of sample size and determination of sampling strategy per study site.

Study Site	Number of Monthly Male Clinic Attendees Per Month	Calculated Sample Size for Study Site (Probability Proportionate to Size)	Systematic Random Sampling Strategy
1	400	(400/900 × 384) 170	(900/400) every 2nd person
2	300	(300/900 × 384) 128	(900/300) every 3rd person
3	200	(200/900 × 384) 86	(900/200) every 5th person
Totals	900	384	

**Table 3 medicina-56-00149-t003:** Outcomes, exploratory factors, and the methods of analysis for each study objective.

Outcome Measures Variable	Criteria for Success/Hypothesis	Exploratory Factors	Methods of Analysis
**Phase 1: Objective 1 To conduct a scoping review on health education programs (HEPs) for men in low- and middle-income countries (LMICs)**			
Improved availability, acceptability, and uptake of health education programs (HEPs) by men in low- and middle-income countries (LMICs).	N/A	Availability, acceptability, and uptake of HEPs.	Thematic content analysis Number studies of reporting outcomes of interest.
**Phase 2: Objective 2 To determine key stakeholder and health care providers’ perceptions on implementation of HIVST in Rwanda**			
Perception	N/A	Key stakeholders and health care provider’s perceptions on the implementation of HIV-self testing	Qualitative Thematic content analysis

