### 2.6. Phase 3: Cross Sectional Survey

#### 2.6.1. Objective 3: To assess HIVST Awareness among Men in Kigali, Rwanda

Design: A cross-sectional study will be employed. One health facility will be selected in each district. Due to the nature of the study design, and assuming that the population is >10,000 and that there is an unknown level of awareness of HIVST among men in Rwanda, the overall sample size will be deduced using the formula below:
(1)$$n=\frac{Z^{2}\times \;\mathrm{pq}\;}{d^{2}}$$
(2)$$n=\frac{1.96^{2}\times \left(0.5\right)\times \left(1-0.5\right)}{0.05^{2}}$$
where *n* = 384 participants.

For HIVST acceptability, assuming the acceptability rate of 94% reported in Kenya [45], the calculated sample size based on the formula above is 241 participants. For the purposes of this study, the desired sample size will be the highest of the two outcome variables. Sample size will not be adjusted for design effect as we will purposively select one tertiary facility in each district hence limiting the issue of error commitment during the recruitment. To determine the minimum sample size per facility, the probability proportionate to size will be used. A sampling frame for each study site will be developed based on the number of the out-patient departments’ male clinic attendees. Table 2 illustrates how sample size will be calculated for each study site and sampling strategy. Enrollment of participants will be by systematic random sampling. All men visiting the facility for the following reasons will be eligible to participate for the study (accompanying someone, visiting someone, or seeking health services). Healthcare workers will be excluded as they are considered implementers of HIVST thus expected to be knowledgeable on the intervention.

Data collection will be conducted using a self-administered semi-structured questionnaire (Supplementary File 2). The questionnaire will address demographic characteristics, health status and sexual behavior, health seeking behavior, and knowledge, attitudes, and perceptions (KAPs) toward HIVST.

Data Source: A semi-structured questionnaire will be employed.

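### Table 2 computes the survey's sampling intervals from the wrong ratio, so they contradict the proportional allocation in the same table

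*Protocol article*

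**What the plan says.** Section 2.6.1 of the protocol article derives a total of "384 participants" for the cross-sectional survey and then divides it between three facilities: "To determine the minimum sample size per facility, the probability proportionate to size will be used". The frame is described as follows: "A sampling frame for each study site will be developed based on the number of the out-patient departments’ male clinic attendees". On selection it states: "Enrollment of participants will be by systematic random sampling". It refers to Table 2 for both the site sample sizes and the sampling strategy.

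Table 2 lists monthly male attendances of 400, 300 and 200 (total 900) and quotas of 170, 128 and 86 (total 384). The last column gives the interval at each site. Site 1 has "900/400) every 2nd person", site 2 has 900/300 and every 3rd person, and site 3 has "900/200) every 5th person".

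On eligibility, section 2.6.1 says "All men visiting the facility for the following reasons will be eligible to participate for the study" and lists men who accompany or visit someone as well as those seeking care.

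**The concern.** A systematic sampling interval is the frame size divided by the number wanted from that frame. Table 2 instead divides the attendance of all three sites by the attendance of the one site. That quantity is the inverse of the site's share of attendance and carries no information about the quota. If the target had been 241 (the figure section 2.6.1 derives for acceptability), the column would read exactly the same.

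Proportional allocation means that every man has the same chance of selection whichever site he attends. The printed intervals give a man at the largest site a one-in-two chance and a man at the smallest a one-in-five chance. The column is a direct field instruction. Followed literally, it disturbs either the site mix behind the pooled awareness and acceptability estimates or the period over which each site is sampled.

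**Working it through.** **Inputs.** From section 2.6.1: Z = 1.96, p = 0.5, d = 0.05, and allocation proportional to size. From Table 2: attendances N = 400, 300, 200 per month; quotas n = 170, 128, 86; intervals 2, 3, 5.

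**Step 1: reproduce the plan's figures.**
- Total: 1.96² × 0.5 × 0.5 / 0.05² = 384.16, which matches 384.
- Quotas: N/900 × 384 = 170.67, 128.00, 85.33, against the printed 170, 128, 86. The differences are rounding and do not matter.
- Printed intervals: 900/N = 2.25, 3.0, 4.5, shown as 2, 3, 5. They reproduce only with this ratio.

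**Step 2: the interval that matches the allocation.** With k = N/n: 400/170 = 2.35, 300/128 = 2.34, 200/86 = 2.33. Up to rounding of the quotas this is one value, 900/384 = 2.34, or a common sampling fraction of 384/900 = 0.43.

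**Step 3: one pass through the monthly frame at the printed intervals.**

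| Site | Yield | Quota | Difference | Share obtained | Share planned |
|---|---|---|---|---|---|
| 1 | 400/2 = 200 | 170 | +30 | 58.8% | 44.3% |
| 2 | 300/3 = 100 | 128 | −28 | 29.4% | 33.3% |
| 3 | 200/5 = 40 | 86 | −46 | 11.8% | 22.4% |
| Total | 340 | 384 | −44 (−11.5%) | | |

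The half-width at p = 0.5 becomes 1.96 × √(0.25/340) = 5.3 points instead of 5.0.

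**Step 4: is rounding to blame?** No. With the unrounded ratios the yield at each site is N/(900/N) = N²/900, that is 177.8, 100 and 44.4, total 322. The ratio makes the yield proportional to the square of site size.

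**Step 5: recruiting until each quota is met.** Men who must pass through: 170 × 2 = 340, 128 × 3 = 384, 86 × 5 = 430. Months needed: 340/400 = 0.85, 384/300 = 1.28, 430/200 = 2.15. The counts and shares are then as planned, but the recruitment windows differ by a factor of about 2.5 (2.15/0.85).

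**Step 6: the corrected interval, rounded down to 2 at every site.** Monthly capacity is 200, 150 and 100. Quotas fill in 170/200 = 0.85, 128/150 = 0.85 and 86/100 = 0.86 months, so the shares are right and the windows coincide.

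**The case against.** A reader might infer that the survey will end up short of 384 and badly skewed towards site 1. The documents do not support that as a firm conclusion. It requires enrolment to stop after exactly one month, and no survey duration is stated. Section 2.6.1 treats the quotas as site minimums, so recruiting until each is filled is a natural reading. On that reading nothing is short or over-weighted, and only the unequal windows remain. The documents give no reason to expect awareness to change materially between about one month and about two. This part of the objection stands.

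Even on the one-month reading the harm is moderate. Precision falls by 0.3 points. The effect on the pooled estimate depends on differences between sites that the protocol does not give. As an assumption, let awareness fall evenly from site 1 to site 3. With a total gap of 10 points, the pooled value above site 3's level is 0.588 × 10 + 0.294 × 5 = 7.35 points, against 0.444 × 10 + 0.333 × 5 = 6.11 under proportional shares. The shift is about 1.2 points, or about 2.5 for a gap of 20. Both lie inside the planned 5-point margin. The sites are also chosen purposively, so the pooled figure is not a probability estimate for Kigali in any case.

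It may also be said that Table 2 is illustrative: the sites are unnamed and the counts are round. The exact yields above should therefore not be read as a forecast. The method would still carry over to the real counts, so this does not rescue the ratio.

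Finally, the frame counts only out-patient attendees while other visiting men are eligible. If those men are counted when taking every 2nd, 3rd or 5th man, monthly yields rise and windows shorten by an unknown amount. This is a separate point. It makes the yields uncertain but leaves the unequal fractions of 1/2, 1/3 and 1/5 as they are.

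**Conclusion.** The interval column is wrong as written. It uses all-site attendance over site attendance where site attendance over site quota is needed, and so contradicts the proportional allocation printed beside it. That conclusion needs no assumption beyond the table itself.

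The consequence is conditional. It is either 340 men with shares of 59/29/12%, if each site makes one monthly pass, or 384 men with the planned shares over windows of about 0.85, 1.28 and 2.15 months, if sites recruit to quota. Both sets of figures rest on Table 2's counts and on only out-patient attendees being counted.

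The error is confined to the Phase 3 survey. A reader might extend it to the pilot randomized trial, but the randomization, outcomes and analysis of Phase 4 do not use these intervals; the only link is that survey findings help to shape the education program. It is a should-fix.

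**What to change.** Replace the last column of Table 2 with site attendance divided by site quota. This gives 2.34 at every site, applied as every 2nd eligible man from a random start at all three sites, stopping when the site quota is reached. State the stopping rule in section 2.6.1. When actual attendances replace the table's counts, recompute the interval with the same formula.

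As a separate minor correction, make frame and eligibility agree: either count all eligible men entering during recruitment hours, or limit eligibility to out-patient attendees.

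The cost is one table column and a sentence or two, with no additional participants. On the table's counts all quotas fill in about 0.86 months. The change needs to be made before survey enrolment begins. If enrolment has already taken place, report the intervals and recruitment dates used at each site, and weight the pooled estimates by the inverse of the sampling fractions if the one-pass version was followed.
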